## Abstract

**Background:**

Cancer is a leading cause of mortality worldwide, with approximately 19.6 million new cases and 10 million deaths reported in 2020. Exercise interventions have demonstrated positive effects on physical and mental health in cancer patients, yet there is limited evidence on the efficacy of tailored, high-intensity exercise programs designed using genomic data. This protocol outlines a study aimed at integrating genomic analysis and personalized exercise interventions to improve health outcomes and reduce cancer-related risk factors. This study aims to evaluate the feasibility and potential impact of a personalized exercise intervention delivered through the EXESALUS mobile application. The program integrates genomic information to tailor exercise regimens for cancer prevention, muscle strength improvement, and quality-of-life enhancement.

**Methods:**

This is a protocol for a 3-month, parallel-group, randomized controlled trial involving 500 participants, including 100 cancer patients undergoing treatment or rehabilitation and 300 non-cancer participants with elevated disease risk. Participants will engage in the EXESALUS program, which includes low-, moderate-, and high-intensity exercise tailored to genomic profiles, supported by exercise counseling and wearable device feedback. Biospecimens (blood, urine, and oral epithelial cells) will be collected at baseline, 6 weeks, and 3 months to assess genomic variations and physiological changes. Primary outcomes include physical performance (SPPB), muscle strength (1RM and peak power), and skeletal muscle mass (DXA). Secondary outcomes will evaluate mental health indicators such as fatigue (FACIT-F), resilience, anxiety, depression, and quality of life.

**Discussion:**

This study will provide a detailed framework for implementing ICT-based personalized exercise interventions that incorporate genomic analysis. The EXESALUS program is expected to highlight the potential of tailored high-intensity exercise as a preventive and therapeutic strategy for cancer patients and individuals at risk of chronic diseases. The findings of this protocol will contribute to the development of precision medicine approaches for cancer prevention and management, emphasizing the scalability and utility of ICT-based solutions in health promotion.

**Trial registration:**

This study was registered in the Korean Clinical Trials Registry (KCT0010187).

Since roughly 2020, the evidence for physical activity and exercise in cancer patients has shifted from negative to positive. Furthermore, the immune effect of killer T cells on CD8 + cells is relatively higher in high-intensity exercise, which reduces fatigue in breast cancer patients [6]; it also inhibits cancer growth by inducing CD8 + cell metabolism [7–9]. In addition, it plays a major role in boosting immunity by increasing natural killer (NK) cell numbers and activity [10,11]. Some chronic diseases (such as pancreatic cancer) are difficult to treat after disease detection, but it is believed that exercise during treatment can improve physical health and quality of life, although more precise exercise programs are needed [12].

Most genomic analysis services are single nucleotide polymorphism (SNP)-based, which means that they predict outcomes using a subset of all genes, thus limiting their predictive accuracy [13]. The occurrence of diseases is due to the multi-layered interaction of several factors, such as hormonal imbalance, environmental factors, and lifestyle, in addition to genes that are congenitally determined. Genetic information alone cannot clearly explain disease onset. With the development of wearable devices and big data analysis technologies, it has become possible to collect and analyze vast amounts of lifestyle and environmental data, which, when combined with personal genomic information, can be used for disease prevention and health promotion to improve quality of life [14]. By accurately predicting an individual’s health risk, suggesting appropriate management plans, and connecting them with health coaching services through the application of appropriate exercise methods, it may become possible to prevent chronic diseases, including cancer, or delay their onset long enough to minimize economic losses for individuals and society.

The current healthcare paradigm is rapidly changing from the existing post-onset treatment method to a prevention-oriented, personalized precision medicine method, and convergence healthcare services using information and communication technology (ICT) have become possible due to the accelerated development of ICT such as mobile networks and applications, Internet of Things, big data, and cloud computing. Therefore, this study aims to identify individual genomic variants, predict cancer prevalence through genomic analysis, and provide an exercise intervention program including high-intensity exercise as a mobile web application to execute personalized exercise, analyze cancer development inhibitory factor expression, and induce muscle strength improvement. Specifically, the purpose of this study is to check the suppressive effect of chronic disease-causing factors, including cancer, based on exercise habits using a mobile web application to predict health risk and establish health-promoting protocols using individual genomic information data.

## Materials and methods

### Study design

This study is a protocol that aims to analyze an individual’s genomic information to predict future health risks and evaluate the health-promoting effects of a personalized exercise program (EXESALUS) based on the results. Additionally, a systematic evaluation of cancer suppressor factor expression, changes in physical strength, and mental health status through a personalized exercise intervention will be conducted.

Participants will follow the EXESALUS exercise program (low-, moderate-, and high-intensity exercise, exercise counseling and guidance, and body information via ICT and wearable devices) for 3 months. Subjects will provide biospecimens (blood, urine, and oral epithelial cells) three times (the beginning of the study, 1 ½ months, and 3 months) to assess genomic information and physiological changes. All biospecimens will be anonymized in accordance with our privacy policy and used for research related to changes in risk markers for chronic diseases, including cancer.

In accordance with the SPIRIT 2013 Checklist.: Recommendations for interventional trial protocol items. (S1 Checklist in S1 File), a Fig 1 is provided to illustrate the time schedule for mental health, physical assessment, and physiological indicator evaluations, along with participant involvement in the study (Fig 1).

**Fig 1 pone.0327947.g001:**
[figure not shown]
SPIRIT-Figure.

### Ethical approval and trial registration

The Institutional Review Board of Yeungnam University granted ethical approval for this study, which has been registered with the Clinical Research Information Service (CRIS), linked to the WHO International Clinical Trials Registry Platform (ICTRP) (KCT0010187). The research data from this clinical study can be assessed on the CRIS platform. (https://cris.nih.go.kr/cris/index/index.do)

To assess mental health, we will use the following scales:

**Resilience**: Wagnild & Young (1993) [15]**Anxiety**: Generalized Anxiety Disorder 7-item Test (GAD-7) [16]**Depression**: Brief Edinburgh Depression Scale (K-BEDS) [17]**Quality of Life**: McGill Quality of Life Scale (MQOL-K) [18]**Fatigue**: Functional Assessment of Chronic Illness Therapy – Fatigue (FACIT-F) questionnaire [19]; the Korean version will be used with prior approval.

This study aims to present new scientific mechanisms that can contribute to physical and mental health promotion and cancer prevention through customized exercise programs and genome-based approaches.

### Subject selection and consent process

#### Recruitment and publicity.

After IRB approval, recruitment will be conducted at all times through posters and promotional materials to recruit subjects on campus and in the surrounding area, including the Yeungnam University Medical Center and Sports Center (S2, S3, S4, S5 in S1 File). Subjects will be included in the study only if they meet the inclusion criteria and voluntarily agree to participate in the study. This study has been approved by the IRB of Yeungnam University (approval number: 7002016-A-2024–069). This study was registered in the Korean Clinical Trials Registry (KCT0010187) on 02/07/2025.

This study is currently ongoing from its approval date, April 16, 2024, to February 28, 2026, as specified in the IRB-approved study plan (S6 in S1 File). The recruitment of participants for this study is planned to be completed by February 28, 2026. Data collection will take place for one year following the completion of participant recruitment, until February 2027. The results of the analyzed data collection are anticipated to occur over the subsequent year, by February 2028. Depending on the number of participants with a history of cancer, the completion timeline may be extended by approximately one year.

The IRB Review Notification (S7 in S1 File) has been included in the supplementary data. Additionally, the confirmation of the independent peer review administered by the funder (S8 in S1 File) has also been provided.

#### Consent to participate in the study.

Prior to the start of the study, the principal investigator and co-investigators will provide the subject with a written and verbal explanation of the study’s purpose and procedures, the privacy and confidentiality of the research materials, the willingness to participate voluntarily, and the potential benefits and risks of the study (S9 in S1 File). After ensuring that subjects fully understand their participation in the research, the study will only proceed if potential participants voluntarily provide written informed consent.

#### Procedure for participation and post-consent.

Consenting subjects will be interviewed and surveyed at a designated location (medical clinic, exercise center, or Yeungnam University Exercise Physiology Laboratory), which will take approximately 1 hour (S10, S11 in S1 File). A suitable time will be arranged with participants.

### Exclusion criteria

Participants will be excluded from the study based on the following criteria:

Subjects who do not voluntarily agree to participate in the study.Subjects who are unable to participate in the exercise program due to physical limitations.Elderly people over 80 years of age or children and adolescents under 20 years of age.Participating researchers who are likely to be disadvantaged by their superiors due to hierarchy within the organization.Subjects who are participating in other studies with similar topics to this study.

To ensure the voluntary participation of the subjects and the fairness of the research process, the above criteria are set to strengthen the objectivity and ethics of the research.

### Subject selection criteria and methods

Subjects will be selected based on the following criteria:

300 registered participants of the Health and Exercise Center who participate in exercise at least once a week and voluntarily agree to participate in the study.100 patients registered at Yeungnam University Medical Center.100 members of the general public who do not participate in exercise.

The total number of subjects is set at 500 for the 3-month study period, and the study will be conducted on subjects who agree to participate after being provided information about the study. Written informed consent will be obtained after the exercise specialist confirms that the subject meets the requirements for participation.

### Rationale for subject selection

In this study, we aim to have a sufficient sample size to compensate for the limitation of our previous study [20], which did not yield significant results due to a small sample size (N = 63) while exploring candidate genes through genome-wide association studies (GWAS). To this end, we plan to recruit at least 500 subjects by setting the power (1-β) at 0.8, the effect size at 0.5, and the significance level (α) at 0.05 using the G-power program.

Additionally, after accounting for non-respondents and voluntary/dropouts, the final study population is expected to be around 400. This sample size will increase the statistical significance of the study and contribute to strengthening the reliability of the findings.

### How will samples be collected?

#### Sample type.

Participants will provide a sample of either urine, oral epithelial cells, or blood on three occasions. The total amount of samples collected will be limited to approximately 15 mL of blood or 300 mL of urine. For oral epithelial cells, we will offer multiple choices based on the participant’s request, and blood will only be collected at the hospital for patients enrolled at Yeungnam University Hospital.

**Oral epithelial cell collection**: A buccal swab will be used to collect oral epithelial cells, and the collection kit will be sent by mail, collected, and referred to a specialized analysis company.**Blood collection**: Subjects will have blood drawn from a vein after an 8-hour fast, and the collected blood and urine will be stored in a −80°C ultra-low temperature freezer in the exercise physiology laboratory at Yeungnam University for the duration of the study before being sent to an analytical laboratory.

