**Fig 3 pone.0327947.g003:**
[figure not shown]
Diagram algorithme.

To evaluate the effectiveness of the exercise intervention, all participants will be measured three times. Data will be de-identified with a numeric code per subject and managed so that only the principal investigator will have access to all participants’ identifying information.

2Exercise interventions

The study will be a 3-month, parallel-group, randomized controlled trial consisting of cancer patients (100) and non-cancer patients (300). The cancer patient group will consist of patients undergoing treatment or post-operative rehabilitation, while the non-cancer patient group will include subjects at more than twice the risk of developing the disease, members of exercise centers, and those who only use ICT apps.

The cancer patient group will be provided with a tailored exercise program to improve cardiorespiratory fitness and muscle strength, which will aim to improve physical function and quality of life.

The **EXESALUS program** is designed so that participants start the exercise intervention within 10 days of enrollment, once their health risk results are confirmed through genetic testing.

If a subject is unable to start the exercise intervention, it will be recorded as a ‘protocol intervention withdrawal.’

Psychological counseling by a clinical psychologist will be provided twice, once before starting the exercise intervention and again at 2-months, to ensure study participation and ongoing motivation.

3-1EXESALUS Exercise Program

The EXESALUS exercise program (http://exesalus.com) is an ICT-based personalized exercise intervention program for health promotion and disease prevention (Fig 4). The program provides a variety of exercises targeting the upper body, lower body, abdomen, and whole body (adjusted by intensity) and provides five workouts per week for 3 months, ranging from low to high intensity, using exercises that are appropriate for the target audience. The goal is to build muscle strength and improve psychological well-being.

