## Discussion

In this study, we will evaluate the impact of personalized exercise intervention on the physical and mental health of cancer patients through the EXESALUS mobile application. The exercise program of EXESALUS is aimed at high-intensity exercise through the animation of 3D avatars to make exercise fun and sustainable. Currently, wearable devices such as smartbands and smartwatches that measure users’ physical activity are available as tools to support this activity; however, wearable devices alone do not make exercise interesting, and it is difficult to perform high-intensity exercise customized to the user.

For people with cancer, research shows that maintaining high-intensity physical activity is necessary. Evidence suggests that CD8+ and NK cells of the immune system, which play an important role in the defense against cancer cells and are activated during exercise, are specifically and significantly activated at high intensity (more so than CD4 + cells) [23–25].

This study is different from existing exercise programs in that it consists of movements designed to increase the heart rate due to high intensity, stimulate lymph nodes and lymph glands, activate related cells (such as T cells) in the lymph that are responsible for immunity, and promote lymphocyte circulation in the systemic lymphatic vessels. Above all, it provides feedback that collects and graphs biometric information to help users apply the right intensity and exercise to their bodies. We planned this study in collaboration with a gene analysis company to anticipate the onset of cancer through gene-based analysis and apply high-intensity preventive exercises to inhibit cancer development.

The results of the study will confirm that a tailored high-intensity exercise program has significant effects on improving physical function, reducing fatigue, and enhancing immune function in cancer patients, which will support the positive effects of exercise on cancer-related health improvements reported in previous studies [26].

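### As described, cancer patients have no concurrent control group, so the cancer-factor aim and the announced conclusion about patients rest on uncontrolled before-after change

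*Protocol article*

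**What the plan says.** **Design and allocation.** The abstract (Methods) and the Exercise interventions section describe a three-month parallel-group randomized controlled trial with 100 cancer patients and 300 people without cancer. On what the patients receive, the latter says: "The cancer patient group will be provided with a tailored exercise program". It describes no split within that group. The Control group section builds the non-exercise group from people whose genetic test puts their disease risk at 2 or less. The heading that mentions randomization is followed only by app enrolment and adjustment of exercise intensity. The Statistics section compares active with not active people.

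**Specimens.** Study design says "Subjects will provide biospecimens (blood, urine, and oral epithelial cells) three times". Sample type says "Participants will provide a sample of either urine, oral epithelial cells, or blood on three occasions", and adds that "blood will only be collected at the hospital for patients enrolled at Yeungnam University Hospital". The Serum Analysis section describes the Trim63, Fos, Col1a and Six2 assays on serum from cancer patients, and adds CRP as an inflammation measure. The section on data collection and individual counseling lists blood samples among the data taken from consenting subjects.

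**Aim and conclusion.** Study design sets out to evaluate cancer suppressor factor expression under the personalised exercise intervention. The Discussion states in advance: "The results of the study will confirm that a tailored high-intensity exercise program has significant effects on improving physical function". It extends this to fatigue and immune function, and names cancer patients as the population.

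**The concern.** An effect of exercise in cancer patients has to be read against similar patients who did not exercise over the same period. The text describes none. The patients are on treatment or recovering from surgery, so function, fatigue and serum markers may move over three months for reasons unrelated to EXESALUS. A comparison with people chosen for low genetic risk would mix the programme with disease status. For the serum factors even that comparison is unavailable if only patients give blood.

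At stake are one stated aim (cancer suppressor factors) and the main conclusion that the article announces about the population it is most concerned with. An analysis plan cannot repair this later, because it cannot create a comparator that was never allocated.

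**Working it through.** **Step 1. Is there a cancer comparator?**

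| Question | Section | Answer in the text |
|---|---|---|
| What do cancer patients receive? | Exercise interventions | The tailored programme, as a group |
| Who is not exercised? | Control group | People with genetic risk of 2 or less |
| How is allocation made? | Section with randomization in its heading | App enrolment and intensity adjustment only |
| What is compared? | Statistics | Active with not active; no contrast within cancer patients |

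The described number of non-exercising cancer patients is zero.

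**Step 2. Who gives blood?** The abstract, Study design and the data collection section point to participants generally. Sample type and Serum Analysis point to hospital or cancer patients. These cannot all stand. If only patients give blood, the serum factors have no comparator of any kind. If everyone gives blood, they have a comparator without cancer, and the cancer comparator is still missing.

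**Step 3. The plan's own figure.** The sample-size section cites "setting the power (1-β) at 0.8, the effect size at 0.5, and the significance level (α) at 0.05" for 500 participants. Reading 0.5 as a standardised mean difference, two-sided, 1:1: n per arm = 2 × (2.80/0.5)² ≈ 63, or 64 with the t distribution. That is 128 in total, and 128/0.8 = 160 with 20% loss. The figure of 500 is not reproduced. That is a separate matter and this point does not depend on it. The inputs are used only in Step 5.

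**Step 4. How often would an uncontrolled test mislead?** From the document: 100 patients, and an implied whole-study loss of (500 − 400)/500 = 20%. Assumed: the same loss applies to patients, leaving 80; natural change δ of 0.1 to 0.3 SD; correlation r between visits of 0.5 to 0.7. None of these three assumptions is in the document, and nothing there ties them to a particular outcome or marker.

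SD of change = √(2(1 − r)), which is 1.000 at r = 0.5 and 0.775 at r = 0.7. Noncentrality = δ/SD of change × √80. Example: 0.3/0.775 × 8.944 = 3.46, and P(Z > 1.96 − 3.46) = 0.93.

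Probability of a significant paired t-test (two-sided 0.05) with no exercise effect:

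| Natural change | r = 0.5 | r = 0.7 |
|---|---|---|
| 0.1 SD | 14% | 21% |
| 0.2 SD | 42% | 63% |
| 0.3 SD | 76% | 93% |

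**Step 5. What would randomising the patients give?** If all 100 were split 1:1 with 20% loss, 40 v 40 remain.
- Detectable difference at 80% power: 2.80 × √(2/40) = 0.63 SD.
- With baseline adjustment, multiply by √(1 − r²): 0.63 × √0.51 = 0.45 SD at r = 0.7; 0.63 × √0.75 = 0.54 SD at r = 0.5.
- Unadjusted power at the plan's 0.5: about 60%. Reaching 80% needs the 128 evaluable, 160 enrolled, of Step 3.

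**The case against.** **It is not settled that only patients give serum.** A reader might infer from Sample type that they are the only blood donors. The sentence can also mean that patients' blood is drawn only at the hospital. The abstract, Study design and the data collection section imply wider collection, and the CRP sentence is not clearly limited to patients. This stands: the patients-only reading follows the more specific operational text, but the document does not establish it. What it does establish is a contradiction.

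**Cancer patients are not expressly barred from the control group.** The risk rule does not exclude them, the trial is called randomized, and Figs 1 and 3 are not shown. The selection criteria also say only 100 patients; the abstract and Exercise interventions are what identify them as cancer patients. This is fair as a caveat. But the text gives the cancer group as a whole the programme, and any allocation by genetic risk would still not be random.

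**The claim is only Discussion prose.** The serum factors are not among the primary or secondary outcomes, and the abstract's stated aim is feasibility and potential impact. This lowers the weight of the serum part. It does not remove the point, because Study design names cancer factors as an aim and the Discussion commits to effects in patients.

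**The illustration depends on assumed values.** It does. A reader might take 93% as the expected error rate. It is the top of the range, and the bottom is 14%.

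**Conclusion.** The point holds in this form. On the text shown, the study is labelled randomized but describes no concurrent comparator for cancer patients. Changes in them, including in the serum factors, are single-arm before-after changes. They can be described, but they cannot be attributed to EXESALUS. The specimen sections contradict each other on who gives blood; resolving that either way leaves the missing cancer comparator untouched.

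The structural conclusion needs no numerical assumption, only that the figures not shown do not describe a different allocation. The size of the risk does need assumptions: with 80 evaluable patients, natural change of 0.1 to 0.3 SD and correlation 0.5 to 0.7, a false signal would appear about 14% to 93% of the time, against a nominal 5%.

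The immune-function part of the announced conclusion has a further gap. No immune-cell measure is described, and CRP is presented as a marker of inflammation.

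**What to change.** **Needed, text only:**
1. Reconcile the abstract, Study design, Sample type, Serum Analysis and the data collection section on who gives which specimen and when. The document does not show which statement is intended, so the sponsor must decide.
2. State in the abstract, the closing aims of the Introduction, Study design and the Discussion that results in cancer patients, including serum factors, are exploratory single-arm changes from baseline. Remove the conclusion announced in the Discussion, including the part on immune function.
3. Correct the description of the cancer cohort as part of a randomized comparison.

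The cost is a weaker claim about cancer patients; no data collection is lost.

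**Optional:** randomise cancer patients not yet allocated between EXESALUS and control. This needs an amendment, and some patients would serve as controls. Even with all 100 it would detect only about 0.63 SD unadjusted (0.45 to 0.54 SD with baseline adjustment), with about 60% power at the plan's effect size of 0.5. The study has been under way since April 2024, so the number still available may be smaller and the power lower.
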